#### **8.1.2 Secondary study parameters/endpoints**

Time to localization: to assess the time to localization, the surgeon will be asked to indicate when he/she is ready to start localizing a targeted LN. The start point is after opening the abdomen, clearance of adhesions, installation of an abdominal wall retraction device. Time will be recorded until the LN is localized, and also until the LN is removed.

Other parameters which will be recorded are: success rate of retrieved individual LNs, overall surgery time from start of surgery until the abdomen is closed again; blood loss; technical failures of the navigation system; and operator satisfaction using standard questionnaires. For health technology assessment, EQ-5D-5L, QLQ-C30, and QLQ-CR29 or QLQ-PR25 will be used before surgery, and at 3 and 12 months

#### **8.1.3 Other study parameters (if applicable)**

We will record body weight, length, age, gender, type of primary tumour, location of primary tumour, size of LN, neoadjuvant treatment, previous pelvic surgery, previous pelvic radiotherapy.

For the patients operated in the navigation arm, targeted LNs which are removed individually will each be evaluated by the pathologist. The pathological findings will be recorded, and correlated with pre-operative imaging parameters. This will provide more insight into prediction of the risk of LN involvement on imaging.

## 8.2 Randomisation, blinding and treatment allocation

Patients will be randomized according to a randomization scheme provided by the Trial bureau through a website. The randomization scheme is blinded from the surgeons and investigators. In the randomization we will stratify for surgical sub-specialization (surgery, urology, gynaecology), since differences in their approach to the targeted lymph nodes might exist. After receiving informed consent, the researcher will visit the randomization website, provide the specialism, and the patient will automatically be assigned a study number and treatment arm.

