## **3. STUDY DESIGN**

This study is designed as a prospective randomized controlled trial (Fig. 1). After giving informed consent, patients will be randomized between conventional surgery without navigation (control arm), and the experimental arm with navigation. Patients will be asked to answer health-related quality of life questionnaires before surgery, and at 3, 6 and 12 months after surgery. Included

patients are part of this study from the first trial related procedure, until 30 days after surgery, even though the questionnaires will take place up to 12 months after surgery. This is because navigation related complications will not take place after the first 30 days. All patients will undergo an additional baseline CT scan with intra-venous contrast in the 2 weeks before surgery. This scan will be used to assess the target LNs. In the experimental arm the CT scan will be used to create a 3D model of the pelvic anatomy including the target LNs.

[figure not shown]

Fig. 1: outline of the study

We have chosen for a randomization setup to have minimum selection bias in the comparison between navigation and conventional surgery. Having a control arm is certainly valid, since the navigation setup is still experimental.

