### 4.2 Inclusion criteria

In order to be eligible to participate in this study, a subject must meet all of the following criteria:

- Age  $\geq 18$
- Scheduled for open abdominal surgery
- Planned removal of at least 1 extra-regional lymph node suspect on imaging, as assessed by the specialist who will perform the operation
- Informed consent

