#### **6.4 Summary of known and potential risks and benefits**

The main risk of the navigation setup is a miss-registration between the actual patient setup and the 3D anatomical model. If this happens, the surgeon can choose a dissection path through critical pelvic structures such as blood vessels, ureters or nerve tissue. To prevent these errors, obvious anatomical landmarks are used to evaluate the accuracy of the system.

Another potential risk is deformation of the patient anatomy. If this happens, the 3D anatomical model is not representative anymore for the actual anatomy. This risk is minimized by patient selection. The mobility of targets (lymph node, recurrence or primary tumour) is assessed before inclusion by evaluation of the location and position changes between different imaging sessions by imaging experts of the study ([name] & [name]). Only targets which are expected to be rigid with respect to the surrounding bony anatomy or large vessels are included.

The major benefit of the navigation setup is improved anatomical insight during surgery. The navigation system provides a view beyond surgical planes. It provides insight in the optimal surgical approach, and aids in decision making between being radical and preventing morbidity. We have the experience that surgery is performed with more certainty and faster for the so far included cases, which were all deemed surgically challenging.

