## 8.3 Study procedures

### Preparation:

- All patients: a baseline CT scan with intravenous contrast will be acquired within 2 weeks before surgery, without bowel contrast. The contrast is used to highlight the arteries (first phase scan) and the ureters (late phase scan). The scan will contain the entire abdomen from the kidneys to the pelvic floor. The scan is acquired in routine clinical practice. **(10 minutes)**
- All patients: the baseline CT scan is registered with other available imaging data (MR/CT/PET), and a researcher will indicate the target lymph nodes. These targets are confirmed with the operating surgeon/urologist. If image interpretation is challenging, a radiologist will be consulted. (Responsibility of the **researcher**)
- Experimental arm: a 3D anatomical model will be generated by the researcher. The total model will contain the arteries, veins, ureters, bones, and if necessary nerves close to the target LNs. The total model will be discussed with the surgeon before surgery. (Responsibility of the **researcher**)

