### In the OR:

- Experimental arm: in the OR the patient will be placed on a dedicated navigation table with a carbon fibre imaging part and the EM field generator will be integrated in the mattress. With the table it is possible to have straight, fixed leg supports, or adjustable

leg holders for French position in bowel surgery. Preparation of the OR table is responsibility of the **researcher**.

- Experimental arm: before surgery, two electromagnetic Patient Trackers will be placed on the back of the patient, left and right from the spinal column. A third Patient Tracker is positioned at the anterior side at the level of the pubic bone. (Responsibility of the **researcher**)
- Experimental arm: after the patient is anesthetised and positioned for surgery a 3D XperCT scan (no contrast fluid used) is acquired. (Responsibility of the **researcher**, **maximum 10 minutes**)
- Experimental arm: the 3D XperCT scan is registered to the planning CT based on bony anatomy. After registration, the locations of the Patient Trackers are determined. Subsequently, the navigation setup is standby for use. (Responsibility of the **researcher**)
- The trial arm of the patient is determined and surgery can start. (Responsibility of the **researcher**)
- Experimental arm: the accuracy of the navigation system is first checked by pointing at bony landmarks, such as the pubic bone, iliac spine, promontory, and/or the large vessels (e.g. the position of the aortic bifurcation or common iliac bifurcations). If needed, the navigation settings can be adapted in the software to improve accuracy. This process will take at most **5 minutes**. (Responsibility of the **surgeon and researcher**)
- All patients: During surgery, the following time points will be noted: start of surgery, surgical field ready for LN localization, LN localized, LN removed, end of surgery. (Responsibility of the **researcher**)
- Experimental arm: At the end of the surgery, the Patient Trackers are removed. (Responsibility of the **researcher**)
- Experimental arm: The surgeon/urologist is asked to fill out the satisfaction questionnaire. (Responsibility of the **researcher**)

After surgery:

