### **11.2 Recruitment and consent**

Patients eligible for the study will be contacted during the pre-operative outpatient clinical appointment by the investigator, nurse practitioner, or treating physician. The investigators will contact the patient, after at least 3 days consideration, to ask if they want to participate. Informed consent will be obtained before the first trial related procedure.

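### The protocol does not fix when the arm is assigned relative to marking the target nodes, and its workable order leaves the list defining the primary endpoint unmasked and unlocked

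*Protocol*

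**What the plan says.** **When the arm is assigned**

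- Section 3: "After giving informed consent, patients will be randomized between conventional surgery without navigation (control arm), and the experimental arm with navigation".
- Section 8.2: "After receiving informed consent, the researcher will visit the randomization website, provide the specialism, and the patient will automatically be assigned a study number". The website gives the arm in the same step. The section says that the randomisation scheme is concealed from surgeons and investigators. It does not say that the assigned arm is withheld from anyone.
- Section 11.2: "Informed consent will be obtained before the first trial related procedure". The baseline CT is an additional scan made for the study, so it follows consent.
- Section 5 describes the extra pre-operative CT, and the marking of targets on it, for patients already randomised to the conventional arm. It adds that no 3D model is made for them.
- Section 8.3, In the OR: "The trial arm of the patient is determined and surgery can start". This line comes after tracker placement, the intra-operative scan and its registration, all labelled experimental arm only.

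**How targets are set.** Section 8.3, Preparation, applies to all patients: "a researcher will indicate the target lymph nodes. These targets are confirmed with the operating surgeon/urologist". The 3D model is then built for the experimental arm and discussed with the surgeon before the operation.

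**What the targets decide.** Sections 8.1.1 and 10.1 define a failed procedure as any target node still present on follow-up imaging.

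**Rigidity of targets.** Section 6.4: "Only targets which are expected to be rigid with respect to the surrounding bony anatomy or large vessels are included". Section 11.4 attributes a similar assessment to the inclusion criteria. The node criterion in section 4.2 is "Planned removal of at least 1 extra-regional lymph node suspect on imaging, as assessed by the specialist who will perform the operation". Neither 4.2 nor 4.3 mentions rigidity or mobility.

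**The concern.** A patient with more marked targets has more chances to fail, so the target list is part of the endpoint definition. Deciding which borderline nodes go on the list involves judgement. If the people making that judgement know the arm, the lists can differ between arms for reasons unrelated to navigation. Randomisation does not protect against this, because the list is made afterwards. Intention-to-treat analysis does not repair it either, because it keeps the patients and the listed nodes but cannot restore nodes that were never listed.

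Fewer targets in the navigation arm would favour navigation and inflate the one-sided error. More targets there would hide part of a real effect. The contradiction over when allocation happens means that a site reading the protocol cannot tell which order to follow.

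**Working it through.** **1. Can the passages be followed together?** Sections 3 and 8.2 assign the arm after consent, and section 5 has CT and marking follow randomisation. The 3D model exists only in the experimental arm and is discussed before surgery, so the arm must be known before the patient reaches the OR. The OR line in 8.3 comes later still, after trackers and a scan that only experimental-arm patients receive. If the arm were first determined there, the earlier steps could not be assigned to the right patients. The only workable order is consent, allocation, CT and marking, or consent, CT and marking, allocation, with allocation before the model is built in either case. Section 5 points to the first of these, but no sentence times allocation against the CT explicitly.

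**2. The plan's own sample size.** Section 4.4 gives 40% vs 16% failures, one-sided alpha 0.05 and 80% power. With unpooled variance:

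n = (1.645 + 0.842)² × (0.40×0.60 + 0.16×0.84) / 0.24² = 6.185 × 0.3744 / 0.0576 ≈ 40.2, rounded up to 41 per arm.

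This reproduces the stated figure. Nothing in this point changes it.

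**3. What a marking difference would do with no navigation effect.** Inputs and assumptions:

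- Mean targets per patient: 71/25 = 2.84 (section 4.4).
- Per-node failure q is the same in both arms, and nodes fail independently. Two values are used: q = 0.17, an assumption that gives about the planned control rate, and q = 4/71 = 0.056, the pilot rate.
- Failure probability per patient with m targets: 1 − (1 − q)^m, with the mean used as m.
- Control arm: 1 − 0.83^2.84 = 41.1% at q = 0.17, and 1 − (67/71)^2.84 = 15.2% at q = 4/71.
- Rejection rate: exact binomial probability that the one-sided pooled two-proportion z-test rejects, 41 per arm.
- The difference in targets per patient is an assumption. The protocol gives no figure.

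| Fewer targets per patient, navigation arm | Navigation failures, q = 0.17 | Rejection rate | Navigation failures, q = 4/71 | Rejection rate |
|---|---|---|---|---|
| 0 | 41.1% | 4.8% | 15.2% | 5.0% |
| 0.1 | 40.0% | 5.9% | 14.7% | 5.7% |
| 0.25 | 38.3% | 8.1% | 13.9% | 6.8% |
| 0.5 | 35.3% | 13.2% | 12.7% | 9.3% |
| 1.0 | 29.0% | 31% | 10.1% | 17% |

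**4. The opposite direction.** Take the planned 40% vs 16% as true. The per-node rate behind 16% at 2.84 targets is 1 − 0.84^(1/2.84) = 0.0595. If the navigation arm has 0.25, 0.5 or 1.0 more targets per patient, its failures rise to 17.3%, 18.5% or 21.0%. Exact power falls from 0.805 to 0.760, 0.711 or 0.609.

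**The case against.** **The order is an inference.** A reader might conclude that the protocol has the targets marked after the arm is known. It does not say so outright. Section 8.2 gives only consent as the starting point, and the OR line taken literally would put marking before allocation. That line may also be meant as a check of the assigned arm at the start of surgery. This stands: marking after allocation is the likelier reading, not a stated fact. The protocol still leaves open a sequence that matters for the endpoint.

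**Eligibility.** A reader might also infer, from the rigidity rule missing in 4.2 and 4.3, that eligibility decisions can differ by arm. The protocol does not support this. Section 6.4 places the mobility assessment before inclusion, the randomisation scheme is concealed, and nothing has eligibility decided again after allocation. What remains is a mismatch between 6.4 and 11.4 on one side and 4.2 and 4.3 on the other. Because the rule in 6.4 is worded per target, any node-level judgement should also be dated.

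**Size.** It is tempting to headline a case such as three targets in one arm and two in the other. At q = 0.17 that gives 1 − 0.83³ = 42.8% vs 1 − 0.83² = 31.1% failures and 29% rejections. It assumes that every navigation-arm patient loses a whole target, about a third of the pilot mean. The protocol offers no basis for a shift that large, or for its direction.

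**Safeguards.** Marking follows one procedure for all patients, uses all available imaging, and brings in a radiologist when interpretation is difficult. Section 10.1 keeps nodes judged inoperable during surgery in the analysis. These narrow the discretion, but none masks the marker or the surgeon, or freezes the list.

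**Conclusion.** The concern holds as a defect of sequence and protection. The allocation passages contradict each other and must be reconciled. Under the order that sections 3, 5 and 8.2 imply, the nodes that define failure are marked and confirmed by people who can know the arm, and nothing locks the list.

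The resulting bias is possible, not demonstrated. For 0.1 to 0.5 fewer navigation-arm targets per patient, the one-sided error would be about 6% to 13% at 17% per node, or 6% to 9% at the pilot rate, instead of about 5%. One whole target fewer gives 31% or 17%. These figures rest on independent nodes, equal per-node failure in both arms and an assumed marking difference. Once lists have been made with the arm known, the analysis cannot undo it, so the order should be settled before enrolment.

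**What to change.** - In sections 8.2 and 8.3, state one order for both arms: consent, baseline CT, targets marked and confirmed by the surgeon, target list locked in the eCRF, then randomisation. Align sections 3 and 5 with it.
- State that no target may be added or removed for the primary endpoint after the lock.
- Delete the OR line on determining the arm, or reword it as confirmation of the arm already assigned.
- Separately, reconcile the rigidity assessment in sections 6.4 and 11.4 with the criteria in 4.2 and 4.3, and record any per-node rigidity judgement before the lock.

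The cost is protocol wording and one eCRF lock field. The sample size stays at 41 per arm. The real downside is scheduling: randomisation moves into the two weeks before surgery, leaving less time to build the 3D model and plan the navigation OR. If that is not workable, having the targets marked and confirmed by readers masked to the arm would protect the list without moving randomisation, but the operating surgeon could then not be the one who confirms it.

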## 8.3 Study procedures

### Preparation:

- All patients: a baseline CT scan with intravenous contrast will be acquired within 2 weeks before surgery, without bowel contrast. The contrast is used to highlight the arteries (first phase scan) and the ureters (late phase scan). The scan will contain the entire abdomen from the kidneys to the pelvic floor. The scan is acquired in routine clinical practice. **(10 minutes)**
- All patients: the baseline CT scan is registered with other available imaging data (MR/CT/PET), and a researcher will indicate the target lymph nodes. These targets are confirmed with the operating surgeon/urologist. If image interpretation is challenging, a radiologist will be consulted. (Responsibility of the **researcher**)
- Experimental arm: a 3D anatomical model will be generated by the researcher. The total model will contain the arteries, veins, ureters, bones, and if necessary nerves close to the target LNs. The total model will be discussed with the surgeon before surgery. (Responsibility of the **researcher**)

### In the OR:

- Experimental arm: in the OR the patient will be placed on a dedicated navigation table with a carbon fibre imaging part and the EM field generator will be integrated in the mattress. With the table it is possible to have straight, fixed leg supports, or adjustable

leg holders for French position in bowel surgery. Preparation of the OR table is responsibility of the **researcher**.

- Experimental arm: before surgery, two electromagnetic Patient Trackers will be placed on the back of the patient, left and right from the spinal column. A third Patient Tracker is positioned at the anterior side at the level of the pubic bone. (Responsibility of the **researcher**)
- Experimental arm: after the patient is anesthetised and positioned for surgery a 3D XperCT scan (no contrast fluid used) is acquired. (Responsibility of the **researcher**, **maximum 10 minutes**)
- Experimental arm: the 3D XperCT scan is registered to the planning CT based on bony anatomy. After registration, the locations of the Patient Trackers are determined. Subsequently, the navigation setup is standby for use. (Responsibility of the **researcher**)
- The trial arm of the patient is determined and surgery can start. (Responsibility of the **researcher**)
- Experimental arm: the accuracy of the navigation system is first checked by pointing at bony landmarks, such as the pubic bone, iliac spine, promontory, and/or the large vessels (e.g. the position of the aortic bifurcation or common iliac bifurcations). If needed, the navigation settings can be adapted in the software to improve accuracy. This process will take at most **5 minutes**. (Responsibility of the **surgeon and researcher**)
- All patients: During surgery, the following time points will be noted: start of surgery, surgical field ready for LN localization, LN localized, LN removed, end of surgery. (Responsibility of the **researcher**)
- Experimental arm: At the end of the surgery, the Patient Trackers are removed. (Responsibility of the **researcher**)
- Experimental arm: The surgeon/urologist is asked to fill out the satisfaction questionnaire. (Responsibility of the **researcher**)

After surgery:

- All patients: within 3 months after surgery, a follow-up scan should be acquired. In most cases a standard clinical follow-up scan is available, either a diagnostic CT scan, or an MR scan of the operated region. If not available, the patient will be scheduled for an extra diagnostic CT scan. (Organization is responsibility of the **researcher**, the **treating physician** is clinically responsible)

#### **8.4 Withdrawal of individual subjects**

Subjects can leave the study at any time for any reason if they wish to do so without any consequences. The investigator can decide to withdraw a subject from the study for urgent medical reasons.

##### **8.4.1 Specific criteria for withdrawal (if applicable)**

Not applicable

#### **8.5 Replacement of individual subjects after withdrawal**

Every subject that withdraws from the study will be replaced by a new one to adhere to the power calculations.

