### 4.4 Sample size calculation

In the current pilot study (N13NAV), a total of 71 targeted lymph nodes were identified in 25 patients. In total, we failed to localize 4 of the 71 lymph nodes, in four separate patients. We therefore expect to have approximately 16% (4/25) failed procedures in the navigation arm ( $p_B=0.16$ ). In the current pilot study, surgeons indicated in at least 6 patients that certain localized lymph nodes would have not been found without navigation. We therefore estimate a failure rate of 40% ( $p_A=0.40$ ) in the control arm ((6+4)/25). In our study setup we test the following hypotheses  $H_0: p_A = p_B$  and the alternative hypothesis  $H_1: p_A > p_B$  (one-sided alpha). The number of

needed patients per arm with an alpha of 0.05 and a power of 80% is 41. Accrual of all patients is estimated to take 36 months (excluding the time to the first follow-up scan for all).

[figure not shown]

Fig. 2: Screenshot of the 3D anatomical model of a patient during navigation surgery in which the arteries (red), veins (blue), ureters (yellow), bones (white), and pathologic lymph nodes (lime) are shown. The tracked pointer is manipulated by the surgeon in the pelvis of the patient, and is shown in real-time within the 3D model (green). In this example a lymph node was localized in between the internal iliac artery, the internal iliac vein and the ureter

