#### **8.6 Follow-up of subjects withdrawn from treatment**

There is no specific follow-up of the patients, except that the first follow-up scan is used to evaluate the primary endpoint. Therefore, study related follow-up of withdrawn patients is not performed.

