## 10. STATISTICAL ANALYSIS

### 10.1 Primary study parameter(s)

The main study parameter is the percentage of failed procedures, where failure is defined as: presence of any residual target lymph node on follow-up imaging.

The final percentage of failed procedures in both arms will be compared using a one-sided two-proportion z-test. The evaluation will be done on intention to treat, including the lymph nodes which are marked as inoperable during surgery due to expected morbidity.

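### Replacing withdrawn patients and not following them up conflicts with the intention-to-treat evaluation, and can bias the primary comparison if withdrawal depends on arm and outcome

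*Protocol*

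**What the plan says.** Four places in the protocol bear on this point.

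- **Section 8.4** lets patients leave at any time for any reason. It also gives the investigator a power to withdraw them: "The investigator can decide to withdraw a subject from the study for urgent medical reasons". Section 8.4.1 sets no specific criteria.
- **Section 8.5**: "Every subject that withdraws from the study will be replaced by a new one to adhere to the power calculations". It does not say at what stage the withdrawal must occur, or which arm the new patient joins.
- **Section 8.6** first notes that the only specific follow-up is the first scan used for the primary endpoint. It then concludes: "Therefore, study related follow-up of withdrawn patients is not performed".
- **Section 10.1**: "The evaluation will be done on intention to treat". The same sentence extends this to nodes that the surgeon judges inoperable because of expected morbidity.

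Three other sections give the context. Section 8.1.1 defines failure as any target node still present on follow-up imaging, read on the first CT or MRI within 3 months of surgery. Section 8.2 assigns the arm after consent, through a website. Section 8.3 says that a routine clinical scan of the operated region usually exists, and that otherwise an extra CT is arranged.

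**The concern.** Intention to treat keeps each randomised patient in the assigned arm, whatever happens later. Sections 8.5 and 8.6 work against this together. No outcome is collected for a withdrawn patient, and another patient is recruited so that the powered number is kept. That purpose is served only if the withdrawn patient does not count towards the 41 per arm.

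Replacement restores the number analysed but not the comparability that randomisation provided. If withdrawals after allocation differ between the arms and are related to nodes being left behind, the observed failure rates are no longer those of the randomised groups. The surgical team cannot be unaware of the arm during the operation. With 41 patients per arm, a few unseen outcomes can matter. An outcome that was never collected cannot be recovered at the analysis stage.

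**Working it through.** **1. The plan's own figure.** Inputs from section 4.4: failure rates 0.40 (control) and 0.16 (navigation), one-sided alpha 0.05, power 80%. The protocol says that the number of "needed patients per arm with an alpha of 0.05 and a power of 80% is 41". With unpooled variance:

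n = (1.645 + 0.842)² × (0.40×0.60 + 0.16×0.84) / 0.24² = 6.183 × 0.3744 / 0.0576 = 40.19, rounded up to 41.

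The figure reproduces and contains no allowance for dropout. Replacement takes the place of that allowance. With the pooled z-test, one-sided power at 41 per arm is 0.789.

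**2. The passages side by side.**

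| Question | Sections 8.5 and 8.6 | Section 10.1 |
|---|---|---|
| Outcome of a patient withdrawn after allocation | not collected by the study | needed |
| Who makes up the 41 per arm | a new patient stands in | every randomised patient |
| Stage of withdrawal | no limit stated | from randomisation on |

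Section 8.2 has the arm assigned after consent. The steps in section 8.3 place the determination of the arm just before surgery starts. On either reading, withdrawal during or after surgery follows allocation.

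**3. Sensitivity of the result.** Section 10.1 says that the percentages "will be compared using a one-sided two-proportion z-test". The statistic is z = (pA − pB) / √[p(1−p)(1/nA + 1/nB)], with p pooled. The counts below are illustrative. The withdrawals added back are assumed to be failures.

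| Control | Navigation | Added back | z | One-sided p |
|---|---|---|---|---|
| 14/41 | 6/41 | none | 2.06 | 0.020 |
| 14/41 | 8/43 | 2 navigation | 1.62 | 0.053 |
| 14/41 | 9/44 | 3 navigation | 1.42 | 0.078 |
| 16/43 | 8/43 | 2 in each arm | 1.92 | 0.027 |
| 16/41 | 7/41 | none | 2.21 | 0.014 |
| 16/41 | 9/43 | 2 navigation | 1.81 | 0.035 |
| 16/41 | 10/44 | 3 navigation | 1.63 | 0.052 |

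The first line written out: 14/41 − 6/41 = 0.1951; p = 20/82 = 0.2439; standard error = √(0.2439 × 0.7561 × 2/41) = 0.0948; z = 2.06.

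The pair 16/41 and 7/41 gives the integers nearest to the planned 40% and 16% (0.40×41 = 16.4; 0.16×41 = 6.56).

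**4. Type I error under assumed withdrawal.** Take no true effect (40% failure in both arms), withdrawals in the navigation arm only, all replaced and not counted. If a fraction d withdraws and a share q of these would have failed, the observed navigation rate is (0.40 − d·q)/(1 − d). With 41 analysed per arm:

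| d | q | Observed navigation rate | One-sided type I error |
|---|---|---|---|
| 5% | 100% | 36.8% | 0.088 |
| 5% | 70% | 38.4% | 0.067 |
| 10% | 100% | 33.3% | 0.154 |
| 10% | 70% | 36.7% | 0.091 |

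The values of d and q are assumptions. The protocol states neither.

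**The case against.** The strongest reply is that no sentence removes withdrawn patients from the analysis set. Recruiting extra patients is compatible with intention to treat, and a replacement would be randomised by the website, not placed in the vacated arm. This stands in part: exclusion is inferred from sections 8.5 and 8.6 read together, and replacement alone would not break intention to treat. The conflict comes from combining replacement with no outcome collection.

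Section 8.6 can also be read as saying only that no additional visits are arranged. Its last sentence favours the stricter reading, and at the least it needs clarifying.

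A reader might infer that the trial will be a per-protocol analysis under another name, with abandoned dissections or unusable navigation dropped from the count. The documents do not support that. Inoperable nodes are expressly kept in the evaluation by section 10.1. Technical failures of the system are a recorded parameter in section 8.1.2, and unusable equipment is not an urgent medical reason under section 8.4. What remains is withdrawal by patients and withdrawal for urgent medical reasons, both of unknown frequency.

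A reader might also infer from the 14/41 vs 6/41 example that two or three replaced patients reverse the conclusion in general. That example is near the threshold, puts every withdrawal in one arm and makes each a failure. Near the planned rates, two such patients leave the result significant.

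Finally, missing-data rules are commonly left to the statistical analysis plan, which is not at hand. This is right for the choice of rule, whose absence is no finding here. It does not answer the point, because an analysis plan cannot supply scans that the protocol says not to follow up.

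**Conclusion.** The point holds as a conflict between stated rules. Patients who withdraw after randomisation have no primary endpoint under sections 8.5 and 8.6 and are in effect substituted, whereas section 10.1 promises to evaluate them as randomised.

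Bias is possible, not demonstrated. It requires withdrawals after allocation that are related to both arm and outcome. In the worst case examined, two unseen navigation failures move p from 0.020 to 0.053. Near the planned rates it takes three to cross 0.05, and then only just (0.052). Two failures in each arm leave the first example significant (0.027). Withdrawals before allocation do no harm to the comparison, but the text does not confine replacement to them.

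The change is still worth making before outcomes are lost. It costs little, and most of the scans exist anyway.

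**What to change.** - **Section 8.5:** limit replacement to patients who leave before the allocation is known. State that any further recruits are added to the analysis set and not substituted into it.
- **Section 8.6:** separate stopping study procedures from refusing use of data. Read the follow-up scan, which is mostly routine, for the primary endpoint unless the patient refuses.
- **Section 10.1:** state that every randomised patient is analysed in the assigned arm.
- **Missing outcomes:** leave the primary rule to the statistical analysis plan, and use missing counted as failure only as a sensitivity analysis. As a primary rule it would dilute the effect. With an assumed 10% missing per arm, 40% becomes 0.9×40 + 10 = 46% and 16% becomes 0.9×16 + 10 = 24.4%. One-sided power at 41 per arm then falls from 0.79 to about 0.66.

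The cost is mainly protocol wording. A few outcomes will be missing and must be handled instead of replaced. If 5% or 10% of the 41 per arm had no outcome and nobody was added, one-sided power would be 0.771 or 0.750 instead of 0.789. Enlarging the sample at the outset as 41/(1 − d) would need 44 or 46 per arm. These rates are assumptions, and reading the routine scans keeps the loss small.
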